#### Primary outcome measure

The primary outcome measure of this study is HRQoL, which will be assessed using a composite score of the 36-item Short Form (SF-36) [41]. HRQoL will be determined at all four measurement moments during the study, which will allow to assess short-term and long-term changes in HRQoL. The effects of the interventions on the SF-36 as overall value and per subcategory will be analysed for timepoints T1, T2, and T3. Subcategories of the SF-36 contain physical functioning, role limitations because of physical health problems, bodily pain, social functioning, general mental health, role limitations because of emotional problems, vitality, and general health perceptions. The validity and reliability of the SF-36 are well established in healthy controls and PwMS [41, 42].

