### Sample size

The sample size of 270 participants is based on a power calculation. A review of earlier studies on the effects of cognitive rehabilitation in MS [14] suggests that we can expect moderate effects (effect size of 0.35) between pre- and post-intervention. Assuming statistical significance of 0.025, a power of 0.80, and an effect size of 0.35, 75 participants per group are needed. A conservative alpha of 0.025 has been chosen to take into account that we compare two interventions with a control group. A correlation of 0.6 between the measures was assumed. Based on previous experiences, a drop-out of 20% over the study period is expected. Therefore, we will include 90 subjects per group to ensure sufficient power. This study will be carried out using an intention-to-treat protocol. Therefore, subjects who withdraw from the study after inclusion will not be replaced.

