### Allocation and blinding

After baseline measurements, participants will be randomly assigned to one of the three conditions with a 1:1:1 allocation using a block randomisation of Research Randomizer (https://www.randomizer.org) to ensure equal group sizes. The block randomisation will not be disclosed to researchers performing measurements and analyses. After receiving informed consent, the involved lifestyle coach or work coach will be informed of the inclusion of the participant in their treatment arm by a researcher who is not involved with the measurements and analyses. Cognitive measures, structural and functional brain measures, neurological-, blood-, and physiological measures will be collected, analysed, and stored under a single-blinded protocol. To achieve single blinding, eligible participants will be randomised and assigned to an intervention by three designated researchers ([name]) who are not involved in data collection and analyses. The researchers who are involved in data collection and analyses ([name]) are not informed about the allocation, nor discuss the intervention with the participants and involved coaches. In addition, researchers who carry out the measurements will explicitly instruct participants not to disclose any information about the intervention they are following.

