Primary analyses will evaluate the effectiveness of the investigated interventions (‘strengthening the brain’, ‘strengthening the mind’) compared to a control group (‘enhanced usual care’) in improving HRQoL (overall score on SF-36). A mixed-model analysis will be performed, with time (T0, T1, T2, and T3) and condition (‘strengthening the brain’, ‘strengthening the mind’, and ‘enhanced usual care’) as fixed factors, and subject as random factor. P-values and estimates of effect sizes will be obtained. Additionally, separate mixed-model analyses will be performed to evaluate the effect of the investigated interventions compared to the control group on cognitive, psychological, physiological, and work functioning, and enhancing the brain’s functional network. Predictors of treatment response will be investigated by adding baseline scores on the biological, psychological, and environmental measures to the mixed-model analyses.

Mediation analyses will be used to study which mechanisms (i.e.., biological, psychological, and environmental) mediate the effect of the interventions on HRQoL. Conditions for mediation will be tested [104]: 1) investigated interventions should affect HRQoL; 2) investigated interventions should affect the presumed mediator; 3) presumed mediator and HRQoL should be related.

The cost-effectiveness analyses will be performed from a healthcare and a societal perspective according to the intention-to-treat principle. Intervention costs will be calculated using a bottom-up micro-costing approach. Missing cost and effect data will be imputed using multiple imputation by chained equations (MICE) with predictive mean matching to account for the skewed distribution of costs. The number of imputed datasets will be increased until the loss of efficiency is smaller than 5% [105]. Each dataset will be analysed separately as described below, after which results will be pooled using Rubin’s rules. Bivariate regression models will be used to estimate cost and effect differences between the intervention groups and the control group, while adjusting for confounders if necessary. Incremental cost-effectiveness ratios will be calculated by dividing the difference in costs by the difference in effects. Statistical uncertainty will be estimated using bias-corrected and accelerated bootstrapping and will be presented in cost-effectiveness planes and acceptability curves. Sensitivity analyses are performed to assess the robustness of the results.

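### The primary mixed model takes T0 as an outcome level and names neither a condition-by-time term nor baseline adjustment, which does not fit the promised effects at T1, T2 and T3

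*Protocol article*

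**What the plan says.** Under Statistical analysis, the protocol article gives the primary model in one sentence: "A mixed-model analysis will be performed, with time (T0, T1, T2, and T3) and condition" (the three arms) "as fixed factors, and subject as random factor". The baseline visit is therefore one of four levels of the outcome. The sentence names no condition-by-time term, no baseline covariate and no contrast to be tested. Baseline scores enter the mixed models only for a different purpose: "Predictors of treatment response will be investigated by adding baseline scores on the biological, psychological, and environmental measures to the mixed-model analyses".

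Two other places bear on this. Primary outcome measure says: "The effects of the interventions on the SF-36 as overall value and per subcategory will be analysed for timepoints T1, T2, and T3". Allocation and blinding says: "After baseline measurements, participants will be randomly assigned to one of the three conditions with a 1:1:1 allocation". So the T0 score is a pre-randomisation measurement, and the effects of interest are at the three later visits.

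**The concern.** Randomisation makes the expected arm difference at T0 zero. In a model with time and condition as main effects, the condition coefficient is one arm difference averaged over all four visits, including the visit at which no effect can exist. Such a model has no term that lets the effect differ by visit, so it cannot supply the effects at T1, T2 and T3. Adding the interaction solves that problem. If the arm means at T0 are left free, however, each effect is a difference in change from baseline, which is less precise than a comparison adjusted for baseline when the correlation is 0.6. The stake is the size and power of the primary HRQoL comparison.

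**Working it through.** **Inputs from Sample size.** Alpha 0.025; effect size 0.35; correlation r = 0.6 between measures; 75 per group needed, 90 recruited, 20% drop-out expected.

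**Assumptions.** Alpha is taken as two-sided because the article does not say; one-sided results are also shown. The 0.35, described as "moderate effects (effect size of 0.35) between pre- and post-intervention", is used as a between-arm difference in SD units, constant over T1-T3. The correlation of 0.6 is applied to every pair of visits. Data are complete unless stated.

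**The plan's own figure.** The article states: "Assuming statistical significance of 0.025, a power of 0.80, and an effect size of 0.35, 75 participants per group are needed". I could not reproduce 75 with a between-arm comparison at that alpha. At two-sided 0.025 the number per group is 156 (one post visit), 125 (change score), 100 (one visit, baseline-adjusted), 83 (T1-T3 mean change) or 58 (T1-T3 mean, baseline-adjusted). At one-sided 0.025 the same designs need 129, 103, 83, 69 and 48. The recruited number is 75 x 1.2 = 90, and 90 x 0.8 = 72 remain after 20% loss. Results are therefore given for 72 and 75 per arm. The sample size itself is a separate matter.

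**Reading A: condition main effect over T0-T3.**
- Expected estimate: (0 + 3 x 0.35)/4 = 0.2625 SD. With complete data this is three quarters of the T1-T3 mean effect.
- Variance factor of a four-visit mean: (1 + 3r)/4 = (1 + 1.8)/4 = 0.70.
- Noncentrality at 72 per arm: 0.2625/sqrt(2 x 0.70/72) = 1.88. Against a critical value of 2.24 this gives power of about 36%.

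**Reading B: condition-by-time contrasts against T0, arm means free at T0.**
- One visit: variance factor 2(1 - r) = 0.80.
- T1-T3 mean minus T0: (1 + 2r)/3 + 1 - 2r = 0.733 + 1 - 1.2 = 0.533.

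**Baseline-adjusted (or arm means constrained equal at T0).**
- One visit: 1 - r^2 = 1 - 0.36 = 0.64. Reading B is 0.80/0.64 = 1.25 times as variable.
- T1-T3 mean: 0.733 - 0.36 = 0.373. Noncentrality at 72: 0.35/sqrt(2 x 0.373/72) = 3.44.

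| Analysis | Expected estimate (SD) | Variance factor | Power, 72 per arm: two-sided (one-sided) | Power, 75 per arm: two-sided (one-sided) |
|---|---|---|---|---|
| A: main effect, T0-T3 | 0.2625 | 0.70 | 36.0% (46.9%) | 37.4% (48.5%) |
| B: T1 change | 0.35 | 0.80 | 54.2% (65.1%) | 56.2% (66.9%) |
| T1, baseline-adjusted | 0.35 | 0.64 | 64.9% (74.7%) | 66.9% (76.4%) |
| B: T1-T3 mean change | 0.35 | 0.533 | 73.7% (82.0%) | 75.6% (83.5%) |
| T1-T3 mean, baseline-adjusted | 0.35 | 0.373 | 88.4% (93.0%) | 89.7% (93.9%) |

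**Simulation of reading A** (1,500 runs each). At 75 per arm with complete data, the mean estimate was 0.260 and power 38%. At 90 per arm with 20% monotone drop-out, the mean estimate was 0.241, a shortfall of 1 - 0.241/0.35 = 31%, because T0 gains weight as later visits are lost. With no true effect at 75 per arm, the mean estimate was about 0 and the type I error 0.029 against 0.025. That gap is about one Monte Carlo standard error: sqrt(0.025 x 0.975/1500) = 0.004.

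**Baseline imbalance under reading A.** A chance T0 difference passes into the estimate with slope (1 + 3r)/4 = 0.70. One standard error of that difference at 72 per arm is sqrt(2/72) = 0.167 SD, which moves the estimate by 0.70 x 0.167 = 0.117 SD. This is variation from one randomisation to the next, and its average is zero.

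**The case against.** The strongest reply is that listing factors does not exclude their interaction, and that the article never says the condition main effect is the test. Several passages point the other way: the effects promised at T1, T2 and T3, the pre-to-post effect size with a correlation between measures in Sample size, and the stated aim of improving HRQoL. On that reading the T0-referenced contrasts are valid and undiluted, and baseline imbalance is subtracted out. It can be added that a journal article leaves the tested contrast and covariates to the full protocol or SAP.

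Much of this stands. A reader might infer that the trial will certainly understate its effect by a quarter, or that power falls from 88% to 36%. The documents do not support either as fact. Both depend on reading the two factors as the whole model, and the second compares the least favourable reading with the best averaged contrast. A reader might also infer that baseline imbalance biases the result; since randomisation follows baseline, it is noise under either reading.

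The reply does not remove the point. The article does specify the model, down to the visit levels and the random term, and that specification does not fit its own list of effects. Nor is baseline adjustment merely an undisclosed detail. T0 is assigned to the outcome and baseline scores are reserved for predictor analyses, so the stated method is less precise than one available from the same data.

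**Conclusion.** The concern holds in a limited form. As written, the primary model does not contain the term that would give the effects at T1, T2 and T3, and it uses T0 as an outcome level without baseline adjustment.

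The cost depends on what was intended. Under the literal reading the estimate is about 0.26 SD in place of 0.35, with about 36% power at 72 per arm. Under the more likely interaction reading the loss is one of precision: 11 percentage points of power at T1 (56% against 67%) and 14 for the T1-T3 mean (76% against 90%), at 75 per arm. These sizes rest on the assumptions listed in the working, chiefly two-sided alpha and a constant between-arm effect of 0.35 SD.

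A reader might infer that this same model, with the same terms, serves every secondary outcome. The article speaks only of separate mixed-model analyses and does not give their terms, so that does not follow.

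**What to change.** Rewrite the primary-analysis sentence so that the outcome is the SF-36 score at T1, T2 and T3, with fixed effects for condition, time, condition x time, baseline SF-36 and baseline x time. Alternatively, keep T0-T3 in the outcome and constrain the arm means to be equal at T0.

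Name the primary contrast of each intervention against enhanced usual care, either at one stated visit or as the T1-T3 average. The choice matters: at 72 per arm, baseline adjustment gives about 65% power at T1 and 88% for the average. Report the T1, T2 and T3 effects from the condition-by-time terms.

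Use the same approach for secondary continuous outcomes that are analysed by mixed model. The cost is wording only: SF-36 is already collected at all four visits, and the article reports that recruitment was still under way, so the text can be settled before analysis. If the full protocol or SAP already specifies such a model, it is enough to bring the article's wording into line with it.

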### Outcome measures

#### Work package 2: Randomized controlled trial

As illustrated in Figs. 1 and 2, measurements in the randomized controlled trial will take place right before the intervention (baseline; T0), directly after the intervention (four months after baseline; T1), at short- and long-term follow-up (10 months (T2) and 16 months (T3), respectively).

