### Statistical analysis

Data will be analysed using R (R Core Team, Vienna, Austria) and Rstudio version 4.2 or higher (PBC, Boston, MA) and/or SPSS version 28 or higher (IBM, Armonk, NY). Analyses will be performed according to intention-to-treat and per-protocol. The main focus of the analyses will be on the intention-to-treat analysis, as this will reduce bias and better represents daily practice. A per-protocol analysis will be performed to evaluate the effect of the intervention on itself, supplementary to the intention-to-treat analysis. Data will be included in the per-protocol analysis if the participant completed the intervention. The alpha level will be set at a statistical threshold of α = 0.05, corrected for multiple comparisons when applicable. GAS will be used to discriminate between responders and non-responders concerning the interventions.

For the outcome cognitive functioning we will calculate a reliable change index (RCI) for each cognitive test based on the enhanced usual care group. Using the RCI scores allows us to correct for learning effects. An RCI score above + 1.64 or below -1.64 is assumed to reflect significant improvement or decline, respectively [5, 103]. The psychological and work functioning data will be obtained via questionnaires and will be analysed as continuous variables together with the physiological data. MRI images will be analysed using FSL (https://fsl.fmrib.ox.ac.uk) and Freesurfer (Charlestown, Massachusetts). Data obtained (atrophy, white matter integrity, task-specific brain activation and brain connectivity) will be exported to Rstudio after which mixed-model analyses will be performed.

Missing data will be minimised by using digital questionnaires, that prompt participants to answer each question before being allowed to proceed. For other outcome measures, multiple imputation will be used for missing baseline and follow-up data. Outliers will be identified and excluded from the main analysis.

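### The SF-36 model names subject as its only random term; if correlation between visits fades over 16 months, the test of change to T3 is anti-conservative and the test of change to T1 loses power

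*Protocol article*

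**What the plan says.** The Statistical analysis section sets out the primary model for the overall SF-36 score: time (T0 to T3) and condition "as fixed factors, and subject as random factor. P-values and estimates of effect sizes will be obtained". It names no random slope, no residual covariance structure and no time-by-condition interaction.

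The Primary outcome measure section makes clear that visit-specific results are wanted: "The effects of the interventions on the SF-36 as overall value and per subcategory will be analysed for timepoints T1, T2, and T3". The visits are unevenly spaced: baseline, four months, then "at short- and long-term follow-up (10 months (T2) and 16 months (T3), respectively").

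The Sample size section gives the only figure on dependence between visits: "A correlation of 0.6 between the measures was assumed". It does not say which visits this refers to, or whether it changes with the gap between them.

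**The concern.** A random intercept with no other structure makes measurements 4 months apart exactly as correlated as measurements 16 months apart. One pooled within-subject variance then sets the standard error of every change-from-baseline contrast. In repeated quality-of-life scores over 16 months, correlation may well weaken with distance. The pooled variance would then be too small for T3 minus T0 and too large for T1 minus T0.

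Both ends matter. The Discussion presents the longer follow-up as a strength that allows long-term effects to be judged, and the long-term change is where false positives would rise. The change measured directly after the intervention is where real effects would be missed.

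**Working it through.** **Inputs from the article.** Visits at 0, 4, 10 and 16 months. Planning figures: "Assuming statistical significance of 0.025, a power of 0.80, and an effect size of 0.35, 75 participants per group are needed". Analysis level: "The alpha level will be set at a statistical threshold of α = 0.05, corrected for multiple comparisons when applicable". Recruitment of 90 per group, with "a drop-out of 20% over the study period is expected", leaves 90 × 0.8 = 72 completers per arm.

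**Assumptions.** Two-sided tests (the article does not state sidedness), equal variance at each visit, complete data, and a range of decay patterns, since the article gives none.

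**The plan's own sample size.** I could not reproduce 75 per group with a standard two-group formula. At two-sided 0.025, 2 × ((2.241 + 0.842)/0.35)² gives 156 for a post-only comparison. Multiplying by 2(1 − 0.6) gives 125 for change, and by 1 − 0.6² gives 100 for baseline adjustment. That is a separate matter, but it explains why the T1 power figures below start near 0.54 rather than 0.80.

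**Formula.** Let r0k be the correlation between T0 and visit k, and r̄ the mean of the six pairwise correlations. For the between-arm contrast in change from T0, with unit variance and n per arm:

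- true variance = 4(1 − r0k)/n
- random-intercept variance = 4(1 − r̄)/n
- ratio q = (1 − r0k)/(1 − r̄)
- actual level = 2[1 − Φ(z/√q)], where z is 2.241 at 0.025 and 1.960 at 0.05.

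If correlation falls with the gap, T0–T3 (the longest gap) lies below r̄ and T0–T1 (the shortest) lies above it. The direction at both ends follows from fading alone.

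**Worked case: linear from 0.7 at 4 months to 0.5 at 16 months.** The six gaps are 4, 10, 16, 6, 12 and 6 months, mean 9. So r̄ = 0.7 − 0.2 × (9 − 4)/12 = 0.617.

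- T3: q = 0.5/0.383 = 1.30. The effective critical value is 2.241/√1.30 = 1.96, so the actual level is 0.050 against 0.025.
- T1: true SE = √(4 × 0.3/72) = 0.129; model SE = √(4 × 0.383/72) = 0.146.
- T1 power for 0.35 SD: Φ((0.35 − 2.241 × 0.146)/0.129) = 0.57 under the random intercept, and Φ(0.35/0.129 − 2.241) = 0.68 with the matching covariance.

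**Range** (T1 power: 0.35 SD, level 0.025, 72 per arm, random intercept versus matching covariance)

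| Correlation pattern | r̄ | q at T3 | T3 level, nominal 0.025 | T3 level, nominal 0.05 | T1 power |
|---|---|---|---|---|---|
| Constant 0.6 | 0.600 | 1.00 | 0.025 | 0.050 | 0.54 vs 0.54 |
| Linear 0.6 to 0.5 | 0.558 | 1.13 | 0.035 | 0.065 | 0.50 vs 0.54 |
| Linear 0.6 to 0.4 | 0.517 | 1.24 | 0.044 | 0.079 | 0.45 vs 0.54 |
| Linear 0.7 to 0.5 | 0.617 | 1.30 | 0.050 | 0.086 | 0.57 vs 0.68 |
| 0.70/0.60/0.50 by visit lag | 0.633 | 1.36 | 0.055 | 0.093 | 0.59 vs 0.68 |
| AR(1), 0.6 per visit | 0.456 | 1.44 | 0.062 | 0.103 | 0.40 vs 0.54 |
| Exponential, 0.6 at 10 months | 0.645 | 1.57 | 0.074 | 0.118 | 0.64 vs 0.89 |

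Simulation (20,000 trials per scenario) agrees with the formula: for example 0.054 for 0.70/0.60/0.50 at nominal 0.025.

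**Tests that are little affected.**

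- *Between-arm difference at one visit.* Its random-intercept variance uses the total variance, which in balanced data is the average of the four visit variances whatever the correlation pattern. Simulated rejection stayed between 0.023 and 0.030 at nominal 0.025.
- *Joint time-by-condition test.* Simulated rejection was 0.052 to 0.073 at nominal 0.05 in the fading scenarios tried.

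**The case against.** **The article is condensed.** Residual covariance, estimation method and degrees of freedom are usual content of an analysis plan, and one that is not shown may state them. This stands in part: independent residuals are implied by the text, not stated. But the article does specify the random part of its primary model, and an analyst following it would fit a random intercept. The point is about that specification, not about a missing detail.

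**The only stated correlation is constant.** With 0.6 throughout there is no inflation. This stands. Decay is an assumption, which is why a range is given.

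**The affected contrast is not named.** The article plans effects at T1, T2 and T3 without saying whether these are changes from T0 or differences at the visit, and the listed fixed factors include no interaction. This also stands. The error falls on the change-from-T0 contrasts that a time-by-condition model would supply. It does not fall on differences at a single visit.

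**Stronger readings to avoid.** A reader might infer that the T3 test rejects twice too often. The documents do not support one figure: at nominal 0.025 the excess is 1.4 to 3 times over the decay patterns tried, and nil at the article's own 0.6. A reader might also infer that the secondary outcomes share the flaw. The article promises separate mixed models for them but does not give their random part.

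**Conclusion.** The point holds in conditional form. As written, the primary model assumes equal correlation across gaps of 4 to 16 months. If correlation fades, the T3 minus T0 contrast between arms is anti-conservative: 1.4 to 3 times nominal at 0.025 and 1.3 to 2.4 times at 0.05. The T1 minus T0 contrast is conservative, at a cost of about 4 to 25 points of power. The direction follows from fading; the size depends on how fast it fades, which the article does not say. These figures also assume equal visit variances and complete data. The change is worth making before analysis because it removes the dependence on an unstated assumption at almost no cost.

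**What to change.** In the Statistical analysis section, replace the subject-only random part of the SF-36 model with a repeated-measures mixed model:

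- time, condition and time-by-condition as fixed effects;
- an unstructured covariance over T0 to T3 (or over T1 to T3 if T0 becomes a covariate);
- REML with Kenward-Roger or Satterthwaite degrees of freedom;
- a stated fallback if it does not converge, such as heterogeneous Toeplitz, or spatial power in actual months, with robust standard errors.

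Read the T1, T2 and T3 contrasts from this model and say whether each is a change from T0 or a difference at the visit. Use the same form for the secondary continuous outcomes analysed by mixed model.

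**Cost.** About a sentence of text. R and SPSS, both already named, can fit it. No new participants or data are needed. There are 10 covariance parameters instead of 2, with 270 participants planned. If correlation is constant, almost nothing is lost (T1 power 0.54 either way). If it fades, the T3 minus T0 interval widens by about √1.13 − 1 = 6% to √1.57 − 1 = 25%, which is the correct width.
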